Myofascial pain syndrome is associated with differentiated, linear band-like hardness of the muscle containing hyperalgesic zones called MTrPs, which cause nociceptive agents such as substance P, potassium and histamine, among many others, to be released. These agents sensitize peripheral nociceptors and nociceptive neurones in the spinal dorsal horn [26]. The MTrP can be defined as a hyperirritable nodule that elicits local and, frequently, referred pain when pressured, situated in a palpable taut band formed by skeletal muscle fibres. It can be found either in the middle part of the muscle fibres (central MTrP) or in the areas where the muscle fibres attach to the tendon (attachment MTrP) [22,26]. With regard to clinical activity, MTrPs can be active or latent. Both cause dysfunction, but only active MTrPs produce spontaneous referred pain [22].

Specific mechanical stimulation of the MTrP, either by snapping palpation of by needling, can elicit a transient and isolated contraction of the fibres of the taut band called local twitch response (LTR) [27]. Despite its specificity, for a number of reasons, such us its low interrater reliability or the difficulties to elicit it in deep muscles, LTR is not considered an essential criterion for diagnosing MTrPs, but just a confirmatory observation [27].

According to Simon's integrated hypothesis [23,28], excessive release of acetylcholine in some dysfunctional motor endplates causes a contracture responsible for the appearance of the taut band in the affected muscle. The capillaries compression caused by the sarcomere shortening reduces local blood circulation, producing ischemia. The availability of oxygen and adenosine triphosphate (ATP) decreases, causing a local energy crisis. The resulting tissue suffering induces the release of sensitizing, substances that activate nociceptors cause pain and contribute to maintaining and further aggravating the dysfunction of the motor endplate [28]. All this would explain the palpatory findings and the increase of local pain sensitivity, that are commonly used as diagnostic criteria for MTrPs [23,29].

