The dysfunction produced by trigger points is characterized by muscle shortening, muscle weakness local or referred inhibition, difficulty in relaxation, lack of coordination, fatigability and delayed recovery, spontaneous pain, pain on vigorous stretching and contracting [30]. Diagnosis of MTrPs is based on physical examination. There are no routine laboratory or imaging tests that objectively substantiate their existence [23], although in recent years specific needle electromyographic examination has become a way to objectively identify MTrPs [31-33]. Even more recently, magnetic resonance elastography [34] or Doppler US associated with US elastography [35] have shown potential to visualize the taut band or the MTrP.

There are currently different treatments for MTrPs [22,36]. The use of the mechanical stimulus of a needle to inactivate and/or eliminate the MTrP is increasing among physical therapists and other health practitioners [28,37] Since no substance is injected, the technique is commonly referred to as dry needling, and it has proven to be as effective as injection in the treatment of MTrPs by mechanically disrupting the MTrP and by activating pain control mechanisms at the spinal dorsal horn level [38].

We can see that diagnosis for SIS, rotator cuff tendonitis and MTrPs are all based mainly on medical history and physical examination [4,10,28].

Some provocation tests to provide evidence of tendonitis are not specific, since they consist of inducing a selective contraction of the muscle being tested and waiting for the pain response [10], which might also give positive results in case that muscle harboured a central MTrP, for pain (either local or referred) on contraction is also a common clinical feature of MTrPs [22,30].

In fact, we can find MTrPs that are prior to tendonitis [39,40]; they can coexist with all degenerative tendinopathy situations.

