### AIMS Regarding Diagnosis

- Identification of any correlation between the existence of active MTrPs and SIS and rotator cuff tendonitis.

- Identification of any correlation between the results of provocation tests for SIS and the existence of active MTrPs.

- Evaluation of the diagnostic reliability of provocation tests for SIS, using MRI and US as standard tests.

- Evaluation of the diagnostic reliability of physical exploration for active MTrPs, using US as a standard evidence.

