### In Relation to Treatment

#### Design: Random clinical trial

The subjects included in the study will be randomized (with a hidden sequence) to two sets of experimental conditions:

1. – Protocolized treatment based on active and passive joint repositioning, stabilization exercises, stretching of the periarticular shoulder muscles and postural reeducation.

2. – The previously described protocolized treatment with the addition of dry needling of active MTrPs on the supraspinatus, infraspinatus, subscapularis and teres minor muscles using Hong's fast-in and fast-out technique, once for each active MTrP and accompanied by a cold spray to reduce the painful post-needling sensation. Only one needling will be performed in each session with an interval of 8 days between sessions.

The purpose of these treatment methods is to isolate the efficacy of dry needling in the treatment of rotator cuff tendonitis and/or SIS.

Training and standardization sessions will be held for both protocols so that the intervention will be the same for all subjects in the study.

The treatment will consist of 10 physiotherapy sessions and the measuring of dependent variables will be made during the initial visit and at the end of the treatment. The final and follow-up measuring will be performed by a blind evaluator.

The sample size is 132 patients (with and error of 0.05 and a power of 80%, if a correlation of 0.25 of the sample size is taken to be 120 patients; expecting a 10% attrition, the necessary sample size would be 132 patients). The patients will be randomized to include 66 subjects in each therapy method.

The study variables related to treatment are shown on the table 2:

**Table 2 T2:** Study Variables Related to Treatment

INDEPENDENT VARIABLE	DEPENDENT VARIABLE	
THERAPY METHOD	Joint restriction by	Flexion-extension movements
		
	digital inclinometer	Abduction-adduction movements
		
		Lateral-medial rotation movements
	
A. Protocolized treatment	Pain on elevation in the scapular plane	VAS scoring
		
		Location of pain
	
B Protocolized treatment + dry needling of MTrPs	Function Constant Test	
	
	Existence of active MTrPs by algometry	Supraspinatus
		
		Infraspinatus
		
		Subescapularis
		
		Teres minor

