## Discussion

This study aims to provide a new vision of shoulder pain, from the perspective of MPS, a syndrome that can account for shoulder pain and dysfunction by itself, but which is perfectly compatible with the coexistence of real conditions affecting the tendons.

As previously mentioned, shoulder pain is an important cause of morbidity with a high prevalence, and a diverse and confusing background from a diagnostic perspective. GPs lack sufficient tools for its diagnosis, since it is based on a clinical examination, without conclusive tests and with few complementary tests, and its treatment (low effectiveness of the treatments described in the literature). This study aims to confirm the information obtained from the very limited literature found on the specificity and sensitivity of the provocation tests the examinater has available. Complex diagnosis complicates treatment, which is fundamental if chronicity and surgery want to be avoided.

Confirmation of the existence of active MTrPs in shoulder pain by means of their visualization with a simple diagnostic technique would allow diagnosis and, consequently, treatment to be improved.

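### Aim 4 judges palpation of active MTrPs against ultrasonography, which the protocol's own background does not support as a reference standard

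*Protocol article*

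**What the plan says.** The fourth aim under AIMS Regarding Diagnosis in the protocol article is "Evaluation of the diagnostic reliability of physical exploration for active MTrPs, using US as a standard evidence". Palpation is the test under study and US is the yardstick.

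The Background describes the two methods as follows:

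- **Physical examination:** "Diagnosis of MTrPs is based on physical examination".
- **Imaging:** "There are no routine laboratory or imaging tests that objectively substantiate their existence". The text then qualifies this. It names needle electromyography as a recent objective method, and reports that magnetic resonance elastography or "Doppler US associated with US elastography [35] have shown potential to visualize the taut band or the MTrP".
- **Active versus latent:** "Both cause dysfunction, but only active MTrPs produce spontaneous referred pain".

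Table 1 (In Relation to Diagnosis) lists MTrP existence by physical examination and by ultrasonography. It does not specify active points, and it does not mention Doppler or elastography.

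In the randomised part, one outcome row of Table 2 is "Existence of active MTrPs by algometry", for four muscles. The only Background text that bears on algometry says that palpatory findings and "the increase of local pain sensitivity, that are commonly used as diagnostic criteria for MTrPs".

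**The concern.** A reference standard has to be closer to the truth than the test it judges. Here the protocol treats physical examination as the established method and US as a developing one, yet Aim 4 has US judge the examination.

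The target is also mismatched. The aim concerns active MTrPs. The protocol's distinguishing mark of the active state is a symptom, and nothing in the document says that US can separate an active point from a latent one. The distinction matters to the study: only active points are needled in the second arm, and latent points in other muscles are listed as confounders.

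If the aim is followed as worded, each site where US is wrong and palpation is right counts against palpation. The study could then discredit or endorse the clinical examination for reasons that have nothing to do with its quality.

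**Working it through.** **1. The plan's own figure.** The protocol gives no accuracy for US or for palpation. Its only computed figure is the sample size, for a correlation of 0.25 with error 0.05 and power 80%. That figure reproduces: (1.960 + 0.842)² × (1 − 0.0625)/0.0625 + 2 = 7.849 × 15 + 2 = 119.7, so 120, and 120 × 1.10 = 132. It does not enter this point, because a larger sample does not remove a bias that comes from the reference.

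**2. The passages side by side.**

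| Aim 4 needs | The protocol provides |
|---|---|
| A standard that establishes MTrPs | Background: no routine imaging test does; examination is the basis of diagnosis |
| A US mode with support | Background: potential reported for Doppler with elastography; Table 1: ultrasonography, mode not given |
| A standard for the active state | Background: active is defined by spontaneous referred pain; Table 1: MTrP existence |

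**3. Size of the bias, by illustration.** All inputs here are assumptions; none is in the protocol. Let p be the share of examined sites truly active, Se and Sp the true sensitivity and specificity of palpation (0.90 and 0.90), and Se_U and Sp_U those of US for an active point. Errors are independent given the true state.

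- Apparent sensitivity = [p·Se·Se_U + (1−p)(1−Sp)(1−Sp_U)] / [p·Se_U + (1−p)(1−Sp_U)]
- Apparent specificity = [p(1−Se)(1−Se_U) + (1−p)·Sp·Sp_U] / [p(1−Se_U) + (1−p)·Sp_U]

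At p = 0.5:

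- US 0.90/0.90: sensitivity (0.405 + 0.005)/0.50 = 0.82, and specificity is the same by symmetry.
- US 0.70/0.70: sensitivity (0.315 + 0.015)/0.50 = 0.66, and specificity is the same.
- US 0.90/0.50, as might happen if US also shows latent points: sensitivity (0.405 + 0.025)/0.70 = 0.61; specificity (0.005 + 0.225)/0.30 = 0.77.

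Apparent sensitivity/specificity of palpation over a range of p:

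| Assumed US accuracy | p = 0.3 | p = 0.5 | p = 0.7 |
|---|---|---|---|
| 0.90/0.90 | 74%/86% | 82%/82% | 86%/74% |
| 0.70/0.70 | 50%/78% | 66%/66% | 78%/50% |
| 0.90/0.50 | 45%/84% | 61%/77% | 75%/65% |

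The true value is 90%/90% in every cell.

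**4. Direction.** Independence of errors drives the downward bias. In the opposite extreme, with US also 0.90/0.90 and both methods wrong at exactly the same sites, they would always agree and palpation would appear 100%/100%. The bias can therefore go either way, and the planned data cannot show which.

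**The case against.** **No accuracy analysis is stated.** Aim 4 speaks of reliability, the data analysis under In Relation to Diagnosis promises correlations, and the Discussion mentions sensitivity and specificity only for the provocation tests. This stands in part: the percentages above show what the aim's wording invites, not a planned output. The wording still makes US the standard, so a low correlation would be read as a fault of palpation.

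**US has some support.** The Background cites work on Doppler US with elastography. That is a fair reason to study US. But it is reported as potential, it concerns the taut band or the MTrP without reference to activity, and Table 1 does not say that this mode will be used.

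**The Discussion might be read as circular.** Its sentence on "Confirmation of the existence of active MTrPs in shoulder pain by means of their visualization with a simple diagnostic technique" could suggest that US is both assumed and on trial. The sentence is conditional and does not name US, so the point does not rest on it.

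**Algometry.** A reader might infer that the protocol itself rules out algometry for active points. It does not. Algometry appears only in Table 2, no passage questions it, and the Background counts local pain sensitivity among the criteria for MTrPs. A cut-off, or a rule combining algometry with examination, may sit in the full protocol. What stands is narrower: that criterion is given for MTrPs in general, while the row's label claims the active state.

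**Conclusion.** The concern holds for Aim 4. By the protocol's own account, US is not a justified standard for active MTrPs, and disagreement with it cannot be attributed to palpation.

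The size is unknown because the accuracy of US is unknown. Under the independent-error assumptions above, true 90%/90% palpation would appear as about 82%/82% to 66%/66% at 50% prevalence, according to whether US is 90%/90% or 70%/70%. The gap widens on one measure when prevalence moves away from 50%. These figures illustrate the mechanism; they do not predict the result.

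A reader might go further and conclude that the aim and the MTrP outcome cannot be answered at all. The document does not support that. Agreement between examination and US can be estimated, and so can the difference between arms in algometry change. What is unsupported is reading the first as accuracy for active MTrPs, or the second, without a further rule, as their existence. Range of movement, VAS pain and the Constant test do not depend on this point.

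The algometry label is a secondary point of lower grade.

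**What to change.** **Aim 4.** Restate it as agreement between physical examination and US on the presence of an MTrP, reported as kappa with positive and negative agreement. Make no reference-standard or accuracy claim for US. Compare US findings between sites palpated as active and as latent only as an exploratory question. If US is to be kept as the standard, the protocol should name the mode and give evidence that it identifies active points.

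**Table 2.** Either tie the algometry row to the Background definition, by stating how spontaneous referred pain enters the classification, or report the row as pressure-pain sensitivity. If a rule already exists in the full protocol, a reference to it is enough.

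**Cost.** Both examinations are already planned, so the change is mainly wording. The price is a weaker diagnostic claim for US. The exploratory comparison needs each palpated site recorded as active or latent, if that is not already done. For Table 2, bringing in the symptom adds an element of judgement to a measured outcome, whereas relabelling gives up the statement that active points have gone.

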### AIMS Regarding Treatment

- Evaluation of the efficacy of dry needling of active MTrPs in the treatment of SIS and rotator cuff tendonitis compared to habitual clinical protocols.

## Design

The project outline is as follows (figure 1):

**Figure 1 F1:**
[figure not shown]
**Recruitment and project outline**.

### In Relation to Diagnosis

Design: Transversal descriptive study

Study subjects: Patients belonging to 5 health centres in the city of Zaragoza (Spain) over the age of 18 who are diagnosed with rotator cuff tendonitis and/or SIS by a general practitioner (GP) and who give their consent after being informed about participation in the study. The minimum number of patients to be recruited is 132.

Inclusion criteria:

- Diagnosis of rotator cuff tendonitis and/or SIS by GP.

- Functional limitation and pain above 50% of the range of movement in flexion, abduction, and elevation in the scapular plane.

Exclusion criteria:

- Previous surgery for SIS

- Great limitation, pain or sudden loss of strength after suffering a traumatism that suggests another serious condition.

- Other red flag signs indicating systemic disease.

- Inability to attend intervention sessions or refusal to participate.

Study variables related to diagnosis are shown on the table 1:

**Table 1 T1:** Study Variables Related to Diagnosis

General variables	Age
	Sex
	Occupation
Pain history	Period of evolution
	Background

Previous treatments	Drug type
	Period administered
	Evolution with medication

Elevation in the scapular plane	Score on Visual Analogical Scale (VAS) Location of pain

Joint restriction (digital inclinometer)	Flexion-extension movements
	Abduction-adduction movements
	Lateral-medial rotation movements

Constant Test	

Provocation tests	Neer manoeuvre
	Jobe's test
	Hawkins test
	Yocum test
	Patte's test
	Gerber test
	Drop arm test. Painful arc test

MTrP existence by means of:	Physical examination
	Ultrasonography

The following confusion variables will be controlled: osteophytes on the lower face of the acromion, existence of latent trigger points on serratus anterior, biceps braquialis and both pectoralis, sports activity and occupation involving lifting of upper limbs above 90° of flexion or abduction.

Data analysis: a descriptive analysis will be made of the defined variables followed by a bivariate analysis by means of Pearson's r, Spearman's rho or Kendall's tau-b correlations. Multivariate analysis will be performed using logistic regression, including the variables that had a significant result in the bivariate analysis. A correlation will be established between diagnosis of SIS and rotator cuff tendonitis, positive provocation tests, existence of active MTrPs and the diagnostic results obtained with US.

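### The diagnostic logistic model selects variables by bivariate significance, with no exception for the confounders the protocol says it will control

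*Protocol article*

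**What the plan says.** Both statements stand in the section In Relation to Diagnosis of the protocol article.

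- After Table 1 comes an unconditional commitment: "The following confusion variables will be controlled: osteophytes on the lower face of the acromion, existence of latent trigger points on serratus anterior". The list goes on to biceps and both pectoral muscles (still latent trigger points), sports activity, and work with the arms raised above 90°.
- The next paragraph, on data analysis, describes "bivariate analysis by means of Pearson's r, Spearman's rho or Kendall's tau-b correlations" and then the model: "Multivariate analysis will be performed using logistic regression, including the variables that had a significant result in the bivariate analysis".

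The article does not say how the named confounders are otherwise to be handled. The inclusion and exclusion criteria do not refer to them, and no matching or stratification on them is described. The later Data analysis section has a covariate rule, but it concerns baseline differences between the randomized groups and does not reach the diagnostic model.

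The diagnostic part has the same size as the trial: "The minimum number of patients to be recruited is 132".

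**The concern.** If a listed confounder is not significant in the bivariate step, the two statements cannot both be followed. The commitment requires adjustment for it, and the model rule gives it no way in. The adjustment set would then depend on p-values from the same data, not on the list declared in advance.

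Bivariate significance is also a poor test of confounding. A confounder whose crude association with the outcome is masked by its relation to the exposure tends to look unimportant, although adjustment for it matters.

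The first two diagnostic aims are associations of active trigger points with the clinical diagnosis and with provocation-test results. A reader told that osteophytes and overhead work would be controlled could receive an estimate that does not account for them.

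**Working it through.** **Inputs.** From Design: Random clinical trial: alpha 0.05 and 80% power; "if a correlation of 0.25 of the sample size is taken to be 120 patients"; a total of 132 once 10% is added for losses. The screening test is a correlation, as stated under In Relation to Diagnosis. The significance level of the screen is not stated; 0.05 two-sided is assumed. The true confounder–outcome correlation r is not in the documents and is varied from 0.10 to 0.30.

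**The plan's own figure.** With two-sided alpha 0.05 and 80% power, (1.960 + 0.842)² = 7.849. For r = 0.25, n = 7.849 × (1 − 0.0625)/0.0625 + 2 = 119.7, which rounds up to the stated 120. Then 120 × 1.10 = 132. The figure reproduces and is not in dispute.

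**Probability that a named confounder is dropped.** Under Fisher's z, a correlation r gives a test statistic with mean m = atanh(r) × √(n − 3) and unit variance. The probability of missing significance is 1 − [Φ(m − 1.96) + Φ(−m − 1.96)]. Example at r = 0.20, n = 132: atanh(0.20) = 0.2027, √129 = 11.358, m = 2.303; the probability of being kept is Φ(0.343) = 0.634, so 0.366 are dropped.

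| Assumed true r | Dropped, n = 132 | Dropped, n = 120 |
|---|---|---|
| 0.10 | 79% | 81% |
| 0.15 | 60% | 63% |
| 0.20 | 37% | 41% |
| 0.25 | 17% | 21% |
| 0.30 | 6% | 8% |

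The 0.25 row is the correlation used to size the study. If four named confounders each had r = 0.20 and the tests were independent, all four would be kept 0.592⁴ = 12% of the time at n = 120.

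**Overstatement among variables that pass.** At n = 132 the threshold is |r| = tanh(1.96/11.358) = 0.171. The mean of the estimated r, given that it passes, follows from the truncated normal distribution on the z scale.

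| True r | Mean r if kept, n = 132 | Overstated by |
|---|---|---|
| 0.15 | 0.231 | 54% |
| 0.20 | 0.249 | 24% |
| 0.25 | 0.274 | 10% |
| 0.30 | 0.308 | 3% |

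These are marginal correlations, not adjusted logistic coefficients.

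**Effect on the exposure estimate.** This was a simulation with n = 120 and 2,000 runs per setting. It used a binary exposure, a binary outcome, and one binary confounder with prevalence 0.4 and an assumed log-odds ratio of 0.7 on the outcome. The confounder entered the logistic model only if its Pearson correlation with the outcome had p < 0.05.

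| Exposure log-OR | Confounder–exposure log-OR | Dropped | Bias, screened | Bias, always included |
|---|---|---|---|---|
| 0 | 1.0 | 55% | 0.056 | −0.003 |
| 0.7 | 1.0 | 39% | 0.030 | 0.006 |
| 0.7 | −1.2 | 73% | −0.091 | 0.022 |
| 0 | 2.0 | 53% | 0.086 | −0.013 |

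The third row is the masked case: the confounder and exposure are negatively related, the mean crude correlation falls to 0.124, and the drop rate is the highest of the four.

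**The case against.** The strongest reply is that the text says the model includes the significant variables, not that it excludes all others. The two sentences could then be read together: named confounders forced in, screened variables added. A journal article may also leave full model specification to a longer document. This has some weight, since the words do not rule that reading out. But the article does more than omit detail. It states a selection rule, makes no exception, and describes no other means of control, so an analyst following it would naturally screen the confounders too.

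It is also fair that this is a descriptive cross-sectional part whose aims are correlations and diagnostic reliability, and that the logistic outcome is not named. That limits the stakes; the randomized comparison is untouched.

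Three stronger readings are not supported:

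- *The confounders will often be dropped.* The documents give no confounder strengths. Omission is frequent for r up to about 0.20 and falls to 17% or less from 0.25 upward at n = 132. Apart from masked confounders, it is most frequent where the association is weak and omission generally biases least.
- *Screening makes intervals too narrow or clearly inflates false positives.* In the simulation above, coverage was 93.9% to 94.8% with screening, against 94.2% to 95.1% with the confounder always included. A separate simulation at n = 132 gave type I error of 5.4% to 5.9% with screening, against 5.0% to 5.3% with full adjustment. No claim on either point is made here.
- *Retained effects are about half again too large.* That is the r = 0.15 case only, and it concerns the marginal correlation.

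**Conclusion.** The point holds as a conflict between a stated commitment and the only stated model rule, with the consequence that the data decide which pre-declared confounders stay in. The size depends on assumed correlations: between 6% and 79% omission per confounder at n = 132 over r from 0.30 down to 0.10. In the simulated settings the bias in the exposure log-odds ratio was modest, 0.03 to 0.09 in absolute value against about 0.02 or less with the confounder always included. Those settings had a single confounder of one assumed strength, so they illustrate the effect and do not bound it. The sample size calculation is unaffected. This is a cheap improvement, not a threat to the trial's main comparison.

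**What to change.** Replace the model sentence with wording to this effect: the logistic model will include active trigger-point status and all confounders listed above, irrespective of their bivariate significance; any bivariate screening applies only to other candidate variables; if outcome events are few, a penalized (Firth) fit will be used.

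Age and sex are not on the article's confounder list, so resolving this conflict does not require forcing them in.

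The cost is a sentence and somewhat wider intervals from a fixed covariate set. The widening was not calculated, because neither the outcome nor its event count is given. If each of the four muscles is coded separately, the fixed set has eight terms: exposure 1, osteophytes 1, latent trigger points 4, sports 1, occupation 1. This is why the penalized fit is worth naming in advance. The 120 and 132 patients stay as they are.

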## Abstract

**Background:**

Rotator cuff tendinopathy and subacromial impingement syndrome present complex patomechanical situations, frequent difficulties in clinical diagnosis and lack of effectiveness in treatment. Based on clinical experience, we have therefore considered the existence of another pathological entity as the possible origin of pain and dysfunction. The hypothesis of this study is to relate subacromial impingement syndrome (SIS) with myofascial pain syndrome (MPS), since myofascial trigger points (MTrPs) cause pain, functional limitation, lack of coordination and alterations in quality of movement, even prior to a tendinopathy. MTrPs can coexist with any degenerative subacromial condition. If they are not taken into consideration, they could perpetuate and aggravate the problem, hindering diagnosis and making the applied treatments ineffective.

The aims and methods of this study are related with providing evidence of the relationship that may exist between this condition and MPS in the diagnosis and treatment of rotator cuff tendonitis and/or SIS.

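### The significance screen for the diagnostic logistic regression lets variables that the protocol treats as effects of trigger points enter as covariates, which can attenuate or distort an adjusted trigger-point association

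*Protocol article*

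**What the plan says.** The data analysis paragraph of the protocol article (In Relation to Diagnosis) works in two steps. First, "a descriptive analysis will be made of the defined variables followed by a bivariate analysis", using Pearson, Spearman or Kendall correlations. Then: "Multivariate analysis will be performed using logistic regression, including the variables that had a significant result in the bivariate analysis". Bivariate significance is the only entry criterion given.

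The variables defined for this part are those of Table 1. Besides age, sex, occupation and history, the table lists, for scapular-plane elevation, "Score on Visual Analogical Scale (VAS) Location of pain". It also lists joint restriction by inclinometer, the "Constant Test", eight provocation tests (Neer, Jobe, Hawkins, Yocum, Patte, Gerber, drop arm, painful arc) and the presence of MTrPs.

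On causal direction, the Abstract (Background) says that "myofascial trigger points (MTrPs) cause pain, functional limitation, lack of coordination and alterations in quality of movement, even prior to a tendinopathy". The Background section, on provocation tests for tendonitis, says that "they consist of inducing a selective contraction of the muscle being tested and waiting for the pain response", and adds that a central MTrP in the tested muscle might also turn such a test positive.

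The section on diagnosis has a separate list of confounders to be controlled: acromial osteophytes, latent trigger points in named muscles, sports activity and overhead occupation. VAS, joint restriction, the Constant score and the provocation tests are not on it. The paragraph closes with a planned correlation between diagnosis, provocation tests, active MTrPs and ultrasound.

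**The concern.** Two of the four diagnostic aims concern an association with active MTrPs: with impingement syndrome and tendonitis, and with provocation test results. Adjusting such an association is useful when the covariates are causes shared by both sides. It misleads when they are consequences of the exposure.

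A significance screen cannot tell the two apart, and it favours variables that track the outcome. On the protocol's own account, pain and loss of function follow from MTrPs. When a provocation test is the outcome, pain VAS and functional scores may lie on the path from MTrP to test result, and the other seven tests are near-duplicates of the outcome. When the imaging diagnosis is the outcome, the same measures may be common effects of MTrP and tendon lesion. Holding them constant can shrink a real MTrP association. Forcing in every listed confounder would not prevent this, because the screen would still admit the clinical measures.

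At stake is the interpretation of the only multivariable step described for the diagnostic part. A weak adjusted coefficient could be reported as showing that MTrPs have no independent relation to the test or lesion, when the model has partly held constant what MTrPs do.

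**Working it through.** **The plan's own figure.** The rule contains no number, but the sample size shows which analysis the study was sized for. Inputs (In Relation to Treatment): correlation 0.25, error 0.05, power 80%. By Fisher's z, two-sided, n = ((1.960 + 0.842) / atanh(0.25))² = 120.3, or 123.3 with the usual +3. The stated 120 is reproduced, and 120 × 1.10 = 132. The size is therefore that of a single unadjusted correlation, not of an adjusted model.

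**The texts side by side.**

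1. Candidate pool: Table 1, with no exclusion stated.
2. Entry rule: bivariate significance.
3. Causal account: MTrPs produce pain and functional limitation, and a provocation test is read from a pain response.
4. Confounder list: separate, and without the clinical measures.
5. Table 2 of the treatment part lists VAS, joint restriction and the Constant test as dependent variables of a trial whose added component is aimed at MTrPs.

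Items 1 and 2 let in variables that items 3 and 5 treat as downstream.

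**Size under assumed structures.** The documents give no effect sizes for these paths, so every input here is an assumption. Simulated logistic regression used N = 120, 600 replicates per scenario and MTrP prevalence 0.5. Three clinical measures each equalled 0.8 × a latent severity level plus 0.6 × noise, and entered only if significantly correlated with the binary outcome. MTrPs raised severity by 0.8 except where stated. Median MTrP odds ratio (OR) and share of significant results, without and with the screened measures:

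| Assumed structure | OR without → with | Significant without → with |
|---|---|---|
| Full mediation through severity | 2.09 → 1.10 | 51% → 5% |
| Partial mediation | 3.01 → 2.01 | 84% → 38% |
| Measures caused by MTrPs and by another cause of the outcome | 2.09 → 1.64 | 50% → 26% |
| Measures caused by MTrPs, no other link to the outcome | 2.78 → 2.61 | 79% → 74% |
| Measures not caused by MTrPs | 2.43 → 2.81 | 68% → 72% |

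On the log-odds scale, the share of the association lost is 1 − ln(OR with)/ln(OR without):

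- full mediation: 1 − 0.095/0.737 = 87%
- partial mediation: 1 − 0.698/1.102 = 37%
- common effect: 1 − 0.495/0.737 = 33%
- no other link: 1 − 0.959/1.022 = 6%

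In the last row the odds ratio rises, as is usual in logistic regression when a predictor of the outcome unrelated to the exposure is added.

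The average number of the three measures passing the screen was 2.98 under full mediation, 2.94 under partial mediation, 1.69 in the common-effect case, 0.34 with no other link and 2.55 when not caused by MTrPs. The screen thus admits the measures most readily where they carry the outcome. The simulation did not enter the other provocation tests as covariates.

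**The case against.** The strongest reply is that the article names neither the outcome nor the exposure of the logistic model. The part is called descriptive, and two of its four aims concern diagnostic reliability. If the model is meant to predict a diagnosis, symptoms and signs are legitimate predictors and the mediator argument does not apply. This stands as far as it goes: the target coefficient is not stated, and a prediction model would be acceptable if labelled as one. It does not remove the point. The other two aims are MTrP associations, the section says confounding will be controlled, and no other multivariable analysis is described for this part.

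A second reply is that the aims on MTrPs ask for correlations, the sample size is for a correlation, and unadjusted correlations are planned. That also stands. A reader might infer that the plan will adjust the MTrP association away and lead to wrongful rejection of the diagnostic hypothesis. The documents do not support this: the entry rule does not touch the unadjusted analyses, and entry of each variable depends on its significance in the data.

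Third, the path from MTrP to test may be specific to the contracted muscle and need not run through VAS on elevation, range of movement or the Constant score. Inclusion also requires pain and limitation, which may narrow the spread of these measures and make them less likely to pass the screen. Both are fair, and they are why the size must be given as a range.

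Finally, covariate lists are often left to a fuller document. Here, however, the article states a rule, and the point is about what that rule admits.

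**Conclusion.** The point holds as a defect in a stated rule with a conditional consequence. If the logistic regression is used to estimate an adjusted association of active MTrPs with a provocation test or with the imaging diagnosis, the rule can admit variables that the protocol itself treats as effects of MTrPs, and the estimate can be attenuated or distorted.

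Under the assumed structures in which MTrPs cause the measures, the loss ran from negligible to near-complete. Which applies cannot be settled from the documents. The conclusion rests on two readings: that the variables submitted to the bivariate step are those of Table 1, and that the article's causal statements are meant as its working hypothesis.

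**What to change.** For each model that estimates an MTrP association, state the outcome and the exposure. Replace the significance screen with a prespecified covariate set: the confounders already listed in that section, plus background characteristics such as age, sex and occupation. State that VAS, pain location, joint restriction, the Constant score and the other provocation tests are not entered in those models, and report them descriptively or as separate outcomes.

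If a diagnostic-prediction model is also intended, label it as such and say that its MTrP coefficient is not to be read as the MTrP association.

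The cost is a sentence or two in the analysis paragraph. No new data or patients are needed, and the planned correlations stay as they are.
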